### Adverse events

Adverse events (AEs) are defined as any undesirable experience occurring to a subject during the study, whether or not considered related to the protocol treatment. All AEs reported spontaneously by the subject or observed by the investigator or his staff will be recorded. Predefined AEs concerning axillary morbidity include seroma, postoperative haemorrhage, wound complication/infection, lymphedema of the arm, lymphedema of the chest wall, neuralgia, paraesthesia, decreased range of motion of the arm or shoulder, muscle weakness of the arm or shoulder, and pain in the arm or shoulder. The severity of the AE is graded according to the NCI/CTCAE 4.0 grading criteria into mild, moderate, or severe, in combination with the degree of limitation in activities of daily living.

A serious adverse event (SAE) is defined as an untoward medical occurrence or effect related to mastectomy, SLNB, completion ALND or axillary radiation therapy that results in death, hospitalisation or prolongation of existing inpatients hospitalisation, or surgery. Other adjuvant treatment is not considered protocol treatment. The local investigator of the participating centre where the SAE occurs is responsible to report the SAE to the central data centre within 24 h. The principal investigators of the study are responsible for SAE assessment and reporting to the accredited medical ethics committee within 15 days. For fatal or life threatening cases, the term will be maximal 7 days for a preliminary report with another 8 days for completion of the report. All SAEs will be followed until they have abated, or until a stable situation has been reached. Depending on the event, follow-up may require additional tests or medical procedures as indicated and/or referral to the general physician or a medical specialist.

### Statistics

#### Endpoints

Regional recurrence rate is the primary endpoint in this study. Secondary endpoints include number of delayed axillary treatment, distant-disease free survival, overall survival, local recurrence rate, other-regional recurrence rate, contralateral breast cancer rate, percentage difference in the administration of postoperative radiation therapy, axillary morbidity rate and quality of life. The events included in the definitions of the different recurrences are provided in Table 1, and are based on the Maastricht Delphi Consensus on Event Definition by Moossdorff et al. [32, 33]. Pathological confirmation of a regional recurrence is mandatory, and recommended in case of other suspicious lesions. All cases with a lesion that is highly suspicious for tumour recurrence on imaging, but not accessible for tissue sampling are presented to the Data Safety Monitoring Board (DSMB) for an independent review.

**Table 1 Tab1:** Definition of a regional, other-regional, local and distant recurrence

Classification	Events included
Regional recurrence	Recurrence in an ipsilateral axillary-, infraclavicular-, or supraclavicular lymph node
Other-regional recurrence	Recurrence in an ipsilateral internal mammary lymph node
Local recurrence	Recurrence in skin or subcutaneous tissue on the ipsilateral chest wall
Distant recurrence	Recurrence in any other location, including recurrence involving the
	sternal bone, or contralateral lymph nodes

Time to event endpoints are defined as the time interval between the date of randomization and the date of first suspicion of the predefined recurrence, or the date of death, whichever comes first, measured in days. Patients in whom recurrence is not observed and are still alive are censored at the date of last follow-up. Death from breast cancer and its treatment, death from a second primary invasive non-breast cancer, and death from other- or an unknown cause are recorded.

Administration of postoperative radiation therapy is registered and the percentage difference between both study arms is recorded. Axillary morbidity rate will be assessed using a validated questionnaire and by predefined adverse events that are recorded by the treating physician. Quality of life will be assessed using validated questionnaires.

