**Design:**

This study is designed as a non-inferiority randomized controlled multicentre trial. Women aged 18 years or older diagnosed with unilateral invasive clinically T1-2 N0 breast cancer who are treated with mastectomy, and who have a maximum of three axillary sentinel lymph nodes containing micro- and/or macrometastases, will be randomized for completion axillary treatment versus no completion axillary treatment. Completion axillary treatment can consist of completion axillary lymph node dissection or axillary radiation therapy. Primary endpoint is regional recurrence rate at 5 years. Based on a 5-year regional recurrence free survival rate of 98 % among controls and 96 % for study subjects, the sample size amounts 439 per arm (including 10 % lost to follow-up), to be able to reject the null hypothesis that the rate for study and control subjects is inferior by at least 5 % with a probability of 0.8. Results will be reported after 5 and 10 years of follow-up.

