#### Sample size

Prior data indicate a 5-year regional recurrence free survival rate of 98 % for the control patient group, and a regional recurrence free survival rate of 96 % is expected for the experimental patient group. A difference of no more than 5 % (delta = 5 %) is considered acceptable, when taking in account the higher morbidity rate caused by completion axillary treatment in the control arm. The expected regional recurrence free survival rates and delta result in a sample size of 399 per arm. Therefore, we will need to study 399 experimental subjects and 399 control subjects to be able to reject the null hypothesis that the rate for experimental and control subjects is inferior by at least 5 % with a probability of 0.8. When taking in account a lost to follow-up rate of 10 %, 878 patients need to be randomized. An annual accrual of 324 patients can be achieved, based on the incidence of women diagnosed with invasive breast cancer in the Netherlands, the rate of patients that is operated on primarily (excluding patients treated with chemo- or hormonal therapy only, or with metastatic disease and frail elderly), the rate of patients with a positive SLN, treatment with mastectomy, the 43 participating hospitals, and an expected accrual rate of 30 %. Therefore, three years will suffice to include the 878 patients.

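### The event rule counts every death, but the primary endpoint's name, Table 1 and the 98%/96% planning rates point to regional recurrence alone; if the rule is followed as written, the 80% power need not hold

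*Protocol article*

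**What the plan says.** All references are to the protocol article.

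- **Name of the endpoint.** Abstract, Design: "Primary endpoint is regional recurrence rate at 5 years". Statistics, Endpoints: "Regional recurrence rate is the primary endpoint in this study".
- **Events included.** Table 1 defines regional recurrence as "Recurrence in an ipsilateral axillary-, infraclavicular-, or supraclavicular lymph node". Death is not listed.
- **Event rule.** Endpoints, below Table 1: time-to-event endpoints run from randomization to "the date of first suspicion of the predefined recurrence, or the date of death, whichever comes first".
- **Censoring rule.** Same paragraph: "Patients in whom recurrence is not observed and are still alive are censored at the date of last follow-up". Causes of death are recorded, but none is excluded from the event definition.
- **Planning rates.** Sample size: "5-year regional recurrence free survival rate of 98 % for the control patient group". The corresponding planning figure without completion treatment is 96%. The margin is 5 percentage points, which the protocol justifies by the extra morbidity of completion axillary treatment.
- **Analysis.** Final analysis: an uncorrected chi-squared test, based on the Kaplan-Meier estimator when data are censored, one-sided at 0.05.

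No section exempts the primary endpoint from the event rule, treats death as a competing event or gives a mortality rate.

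**The concern.** The endpoint that was sized and the endpoint that the rule defines appear to be different quantities. Read literally, the rule turns the primary endpoint into regional recurrence or death from any cause. The planning rates look like regional recurrence alone: the Background reports 1.0%, 0.9% and 1.1% in the study arms of three earlier trials. If 98% were the composite, recurrence and all deaths together could reach only 2% over 5 years in controls. These patients are node-positive, Study population states no upper age limit, and one randomization stratum is age above 75.

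Two things are at stake. Deaths unrelated to axillary treatment add variance without adding between-arm information, so power falls. And a margin argued as a trade of regional control against morbidity would be applied to a quantity that includes mortality. Local and other-regional recurrence, also defined in Table 1, come under the same rule.

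**Working it through.** **Inputs.** From Sample size: 98% and 96% at 5 years, margin 0.05, power 0.8, 399 per arm. From Final analysis: one-sided alpha 0.05 (z = 1.645; z for 80% power = 0.842). Five-year mortality *m* is not in the documents. It is assumed equal in both arms and shown over a range.

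**Step 1, the plan's own figure.**
n = (1.645 + 0.842)² × (0.98×0.02 + 0.96×0.04) / (0.05 − 0.02)² = 398.4, rounded up to 399 per arm. The stated figure is reproduced, with 80.0% power.

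**Step 2, the rule as written.** Take 2% and 4% as recurrence-only rates and death as independent of recurrence. The event-free rates become pC = 0.98(1−m) and pE = 0.96(1−m), and

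power = Φ( (0.05 − (pC − pE)) / √[(pC(1−pC) + pE(1−pE))/399] − 1.645 ).

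At m = 5%: pC = 0.931, pE = 0.912, difference 0.019. The standard error is √[(0.0642 + 0.0803)/399] = 0.0190, so power = Φ(0.031/0.0190 − 1.645) = 49.4%.

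The share of events that are deaths without regional recurrence, arms pooled, is 1 − 0.06/[(1−pC) + (1−pE)].

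| Assumed m | pC / pE | Power at 399 per arm | n per arm for 80% | Power if the difference stays 2 points (0.98−m, 0.96−m) | Deaths as share of events |
|---|---|---|---|---|---|
| 0% | 0.980 / 0.960 | 80.0% | 399 | 80.0% | 0% |
| 1% | 0.970 / 0.950 | 70.6% | 516 | 69.9% | 24% |
| 2% | 0.960 / 0.941 | 63.3% | 628 | 61.8% | 39% |
| 3% | 0.951 / 0.931 | 57.5% | 734 | 55.6% | 49% |
| 5% | 0.931 / 0.912 | 49.4% | 930 | 46.7% | 62% |
| 10% | 0.882 / 0.864 | 38.7% | 1338 | 35.0% | 76% |

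Simulation with 200,000 runs per scenario agrees within about 1 point: 79%, 64%, 50% and 39% at m = 0, 2, 5 and 10%. With no loss to follow-up (439 per arm), power is 53% at m = 5% and 41% at m = 10%.

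**Step 3, where deaths become the majority.** The share reaches one half when (1−pC) + (1−pE) = 0.12. That is 2 − 1.94(1−m) = 0.12, so m = 1 − 1.88/1.94 = 3.1%.

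**Step 4, a more favourable recurrence assumption.** With 1% regional recurrence in both arms, pC = pE = 0.99(1−m). At m = 5% both rates are 0.9405, the standard error is √(2×0.9405×0.0595/399) = 0.01675, and power = Φ(0.05/0.01675 − 1.645) = 91%. At m = 10% it is 73%.

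**The case against.** The strongest reply is that the death clause sits in a general paragraph on time-to-event endpoints, which also has to serve survival endpoints. The primary endpoint is called a recurrence rate throughout, Table 1 omits death, and the first-named test is a plain chi-squared test. On that reading the primary endpoint is a 5-year proportion with regional recurrence, and 80% power is intact. This stands as a possible reading. It does not clear the text: Sample size plans on recurrence-free survival, and Final analysis moves to Kaplan-Meier once data are censored. That needs an event and a censoring rule, and the document supplies only the one that counts deaths. If deaths are not meant to count, the rule is wrong for the primary endpoint.

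Three stronger inferences are tempting, and the documents do not support them:

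- *That the power is certainly lost.* This requires the composite to be what is analysed and 98%/96% to be recurrence-only rates. The latter is inferred from their scale; the prior data behind them are not shown. The size of the loss also depends on the planned 2% versus 4% (Step 4).
- *That deaths dominate the primary endpoint.* This needs 5-year mortality above about 3%, and no figure is given. Metastatic disease is excluded, and the accrual estimate leaves out frail elderly patients, although that is not an eligibility rule.
- *That the contralateral cancer rate also becomes a composite with death.* The rule speaks of a predefined recurrence, and Table 1 has no category for contralateral breast cancer.

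A later analysis plan could add competing-risk detail, but the point here is a conflict between stated passages rather than an omission.

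**Conclusion.** The point holds as a contradiction in the definition of the primary endpoint, with a conditional effect on power. The name and Table 1 say regional recurrence; the event and censoring rules say regional recurrence or death from any cause; the planning rates fit the former far better than the latter. If the rule is followed as written and 98%/96% are recurrence-only rates, the stated 80% is not delivered at the planned rates: power is about 71% at 1% mortality and 39% at 10%, assuming equal mortality in both arms. If true recurrence is nearer 1% in both arms, power stays above 80% at 5% mortality and falls below it at 10%. Whatever the mortality, the contradiction must be resolved, because it decides what the 5-point margin is a margin on.

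**What to change.** In Endpoints, define the primary endpoint as the 5-year cumulative incidence of regional recurrence per Table 1, with death without regional recurrence as a competing event. In Final analysis, estimate it with the Aalen-Johansen estimator and test the between-arm difference against the 5-point margin. In Sample size, state that 2% and 4% are cumulative incidences of regional recurrence; 399 per arm and 80% power then stand. Treat local and other-regional recurrence the same way. Keep regional-recurrence-free survival including death as a secondary endpoint.

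This costs wording only: causes of death are already recorded, the existing rule already uses the date of death, and no extra patients are needed.

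If the composite is preferred as primary, restate its planning rates with deaths included, the justification of the margin for that quantity, and the power. That route may not be free: at the planned recurrence rates, 80% power would need about 516 per arm at 1% mortality and 930 at 5%.

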#### Sample size

Prior data indicate a 5-year regional recurrence free survival rate of 98 % for the control patient group, and a regional recurrence free survival rate of 96 % is expected for the experimental patient group. A difference of no more than 5 % (delta = 5 %) is considered acceptable, when taking in account the higher morbidity rate caused by completion axillary treatment in the control arm. The expected regional recurrence free survival rates and delta result in a sample size of 399 per arm. Therefore, we will need to study 399 experimental subjects and 399 control subjects to be able to reject the null hypothesis that the rate for experimental and control subjects is inferior by at least 5 % with a probability of 0.8. When taking in account a lost to follow-up rate of 10 %, 878 patients need to be randomized. An annual accrual of 324 patients can be achieved, based on the incidence of women diagnosed with invasive breast cancer in the Netherlands, the rate of patients that is operated on primarily (excluding patients treated with chemo- or hormonal therapy only, or with metastatic disease and frail elderly), the rate of patients with a positive SLN, treatment with mastectomy, the 43 participating hospitals, and an expected accrual rate of 30 %. Therefore, three years will suffice to include the 878 patients.

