#### Final analysis

Primary and secondary endpoints will be analysed per protocol and in the intention to treat population after 5 and 10 years of follow-up. Primarily, uncorrected chi-squared statistics will be used to evaluate the null hypothesis. The chi-square test will be based on the Kaplan-Meier estimator, in case of censored data. Additionally, cox proportional hazards models and Kaplan Meier estimates will be used to analyse the outcome of both groups and to assess the univariable and multivariable association between prognostic variables, treatment and events, using the stratification factors. All statistical tests are 1-sided and a *P* value of 0.05 or less is considered statistically significant.

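### With about 8 versus 16 expected recurrences, 399 per arm does not give both a true one-sided 5% error and 80% power: a test that holds 5% has about 75% power

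*Protocol article*

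**What the plan says.** Under Sample size, the protocol article gives the planning rate for the control arm: "Prior data indicate a 5-year regional recurrence free survival rate of 98 % for the control patient group". For the study arm it plans on a figure two points lower: "a regional recurrence free survival rate of 96 % is expected for the experimental patient group". With a margin of 5 percentage points it concludes "The expected regional recurrence free survival rates and delta result in a sample size of 399 per arm". The aim is to reject the null hypothesis that the study arm "is inferior by at least 5 % with a probability of 0.8". Ten per cent is added for loss to follow-up, giving 878 patients; the Abstract (Design) puts it as "the sample size amounts 439 per arm".

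Under Final analysis, the null hypothesis is evaluated primarily with an uncorrected chi-squared statistic. For incomplete follow-up, "The chi-square test will be based on the Kaplan-Meier estimator, in case of censored data". On sidedness the section says "All statistical tests are 1-sided". Its threshold is a P "value of 0.05 or less is considered statistically significant". The article does not say which variance the statistic uses.

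**The concern.** The stated rates imply 399 × 0.02 = 7.98 control and 399 × 0.04 = 15.96 study-arm recurrences. The sample size formula treats the observed difference as normal, with each arm's variance taken at its own rate. With so few events that variance is unreliable in a particular direction: when the study arm happens to show few recurrences, both the difference and its estimated standard error shrink, and non-inferiority is declared too readily.

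The trial's main conclusion rests on one non-inferiority test. If that test uses this kind of variance, omission of axillary treatment is wrongly declared non-inferior somewhat more often than the stated 5%. If it uses one that holds 5%, the stated 80% power is not reached. Either way, one of the two stated properties fails. This is separate from whether the 5-point margin is written into the chi-squared statistic; the check below assumes that it is.

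**Working it through.** **Inputs.** From Sample size: control recurrence 2%, study-arm recurrence 4%, margin 5 points, power 0.80, 399 evaluable per arm. From Final analysis: one-sided 0.05. Assumption: the 2% and 4% are regional recurrences only.

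**1. Reproduce the plan's figure.** Unpooled large-sample formula:

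n = (z₀.₉₅ + z₀.₈₀)² × [p_C(1 − p_C) + p_E(1 − p_E)] / (margin − expected difference)²

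= (1.645 + 0.842)² × (0.98 × 0.02 + 0.96 × 0.04) / (0.05 − 0.02)² = 398.4, rounded up to 399.

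Then 399 × 1.10 = 438.9, so 439 per arm and 878 in all. The arithmetic is right.

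**2. Exact behaviour at 399 per arm.** Every pair of recurrence counts was enumerated and weighted by its binomial probability. For the error, the true difference was set at exactly 5 points; for power, at 2% versus 4%.

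| Control recurrence | Error, unpooled or pooled z | Error, Farrington-Manning score |
|---|---|---|
| 0.5% | 6.8% | 4.7% |
| 1% | 6.6% | 4.8% |
| 2% (planned) | 5.9% | 4.9% |
| 3% | 5.7% | 5.0% |
| 4% | 5.6% | 4.9% |
| **Power at 2% v 4%** | **79.3%** | **74.9%** |

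The unpooled and pooled versions give the same figures here. The Miettinen-Nurminen score test gives the same figures as Farrington-Manning.

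**3. Is the shortfall peculiar to the score test?** No. By the Neyman-Pearson lemma, any test that holds 5% everywhere on the 5-point boundary has power at 2% versus 4% no greater than the most powerful test against any single boundary point. The least favourable point found (1.4% versus 6.4%) gives an upper bound of 75.6% at 399 per arm. With all 439 per arm followed, the score test has 78.6% and the bound is 79.2%. The score test reaches 80% at about 460 per arm before loss (79.8% at 455, 80.3% at 463).

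**4. Kaplan-Meier version.** Simulated 5-year Kaplan-Meier difference with Greenwood variance (60,000 trials, exponential times assumed):

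- 399 per arm, no loss: error 5.8% at 2% control recurrence and 6.6% at 1%.
- 439 per arm, 10% lost by 5 years: error 5.9% and 6.4%. Nominal power is 80.6%, but at that inflated error. Recalibrating the critical value to give 5% at one control rate lowers the power to 78.3% (calibrated at 2%) or 76.5% (calibrated at 1%).
- A score version in the 439-with-loss setting (smaller simulation of 8,000 trials per setting) had error of about 4.9% and power of about 76%.

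**5. What it means at the boundary.** Take 8 control and 19 study-arm recurrences. The rates are 8/399 = 2.005% and 19/399 = 4.762%, a difference of 2.757 points, which is 2.243 points inside the margin.

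- Unpooled: SE = √[(0.04762 × 0.95238 + 0.02005 × 0.97995)/399] = 0.01276, so z = 0.02243/0.01276 = 1.76, above 1.645: non-inferior.
- Score: the rates constrained to differ by 5 points are 6.556% and 1.556%, so SE = √[(0.06556 × 0.93444 + 0.01556 × 0.98444)/399] = 0.01385 and z = 1.62, below 1.645: not shown.

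So the limit at 8 control recurrences is 19 or 18. At 4 it is 16 or 15; at 12 it is 22 for both.

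**The case against.** The strongest reply is that nothing here is miscalculated. A reader might infer from the point that 399 is an arithmetic error; it is not, and the formula is a standard one. That part of the reply stands in full.

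Second, Final analysis names no variance. "Uncorrected" rules out a continuity correction, and a score statistic with the margin built in could also be called an uncorrected chi-squared. The choice may be made in an analysis plan that is not shown. This stands for the error: a reader might infer that the trial's real one-sided error is 6% to 7%, and the document does not support that. The excess arises only under an unpooled, pooled or Greenwood variance. Even then it is 5.9% at the planned control rate, less at higher rates, and above 6% only when control recurrence is below 2%. Lower rates are conceivable, since the Background reports 0.9% to 1.1% in the study arms of earlier trials, but those patients mostly had breast-conserving therapy.

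The same reply does not rescue the power. A later choice of a score or exact test would restore 5% but leave about 75% at 399 evaluable per arm. Nor does the 10% allowance cover the gap: with no loss at all the bound stays below 80%.

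Third, the effect is small beside the uncertainty in the planning rates. With the score test at 399 per arm, power is 95% at 2% versus 3% and 99% at 1% versus 2%. This is fair. It argues against calling the design inadequate, not against stating the power correctly at the protocol's own planning point.

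**Conclusion.** The concern holds in a limited form. The 399 is correctly derived from its formula, but at about 8 versus 16 expected recurrences a true one-sided 5% error and 80% power cannot both be had with 399 evaluable per arm.

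- **Unconditional on the choice of test:** a score test that holds 5% has 74.9% power at 98%/96%, and no test holding 5% over the whole boundary exceeds 75.6%. The score test has about 76% with 439 randomised and 10% censored, and 78.6% with no loss.
- **Conditional on an unpooled, pooled or Greenwood variance with the margin in the statistic:** error of about 5.9% at the planned 2% control recurrence, 5.6% at 4%, and 6.6% to 6.8% at 1% to 0.5%.

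This amounts to roughly 1 to 2 points of error or 5 points of power, and at most one recurrence at the decision boundary in the cases checked. It is worth correcting but does not undermine the design.

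The figures treat 98% and 96% as recurrence only. The Endpoints section also counts death in its time-to-event definition; if deaths enter the primary analysis, the event numbers and all these percentages change. The simulated figures further assume exponential recurrence and loss.

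**What to change.** Under Final analysis, specify the primary test as a one-sided restricted-variance (score) non-inferiority test of the 5-point difference, such as Farrington-Manning or the matching Miettinen-Nurminen interval. For censored data, specify an equivalent version for the 5-year Kaplan-Meier rates, with a check that it holds 5%. Feeding the score test the Kaplan-Meier rates and effective sample sizes is one option.

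In the Abstract (Design) and under Sample size, keep 878 patients and restate the power at 98%/96% as about 75% with 399 evaluable per arm (about 75% to 76% allowing for the information from censored patients).

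The cost is wording and a slightly less favourable stated power; no extra patients, visits or data are needed. Fixing the test before outcomes are seen also removes a choice of variance that could decide a borderline result.
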